### Outcome Measures

The primary outcome will be the presence of corpus luteum with a characteristic “ring of fire” appearance on the transabdominal ultrasound on the day of embryo transfer.

The secondary outcomes consist of the number of clinic visits required per patient undergoing this protocol, the biochemical pregnancy rate defined as the detection of βhCG in serum or urine [14], and the clinical pregnancy rate defined as the ultrasonographic visualization of one or more gestational sacs [14].

### Randomization

This is a pilot prospective cohort study without randomization.

### Intervention: P4mNFET Protocol

Participants will undergo active treatment for 2-8 weeks, with a follow-up period of up to 12 weeks or gestation. For a patient with a 28-day menstrual cycle, on days 10-12 (Figure 1), a transvaginal ultrasound will be performed to evaluate for an appropriate endometrial thickness of 7.0 mm and a mean follicle diameter of 14.0 mm. If these ultrasound criteria are met, the patient will undergo blood tests for estrogen, LH, and P4 on the same day; should levels of P4 be under 5 nmol/L, exogenous P4 supplementation via vaginal pessary will then commence on the same day, with FET scheduled 120-125 hours post P4 administration. P4 pessary, ORIPRO (Orion Laboratories Pty Ltd T/A Perrigo Australia, Balcatta, Western Australia), at a dose of 200 mg twice daily, will be the only form of LPS for patients undergoing P4mNFET. Following FET, serum hCG will be taken 10 days later. If positive, LPS via P4 pessary at 200 mg twice daily will continue to 8 weeks’ gestation with a pregnancy scan between 6-7 weeks. If negative, the patient will be advised to cease LPS. In the instances where P4 levels are greater than 5 nmol/L, the patient will be removed from the study.

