**Objective:**

This study aims to assess the feasibility of a progesterone-modified natural cycle protocol for FET. The primary outcome will be the presence of a corpus luteum on ultrasound scans on the day of embryo transfer. The secondary outcomes will include the number of clinic visits required per patient undergoing the protocol, biochemical pregnancy rate, and clinical pregnancy rate.

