### Participants

The study population will consist of 20 women undertaking FET cycles at the Public Fertility Care of The Royal Women’s Hospital (RWH), Melbourne, Australia. The recruitment process will commence at this location, whereby clinicians and nursing teams will be invited to screen the patients they interact with for eligibility for the study. These staff members will be trained on appropriate screening according to the study protocol and will be delegated by the principal investigator. Eligible patients will then be approached for study by team members who are not directly involved in potential participants’ clinical care and, therefore, will not have had any clinical interactions with the participant. All patients will be provided with a patient informed consent form (Multimedia Appendix 1) to ensure they are familiar with the protocol requirements and understand their rights as participants. Additionally, they will be provided with a patient information document created by the research team (Multimedia Appendix 2) to assist with patient education surrounding the use of the P4 pessary during the study.

Inclusion criteria consist of women with regular cycles defined as 21-35 days, women younger than 40 years at the start of a cycle, and women whose BMI ranges from 18 to 35, inclusively.

The exclusion criteria include anovulatory women, women who are 40 years or older at the start of the cycle, and women who have preexisting contraindications to exogenous P4 supplementation, such as those with liver disease or thromboembolic disease. The exclusion criteria will also include the use of additional LPS (eg, subcutaneous), women with uterine pathology, including congenital malformations of the female reproductive tract, endometrial polyps, intrauterine adhesions, adenomyosis, and leiomyoma. Regarding the retrospective element of the study, patients for whom inclusion criteria information is lacking will not be included in the study.

The control group will consist of retrospective data from 20 women, matched against inclusion and exclusion criteria, within the Public Fertility Services of the RWH data bank. These controls would have undergone tNFET at the service provider within the preceding 12 months of the study start date.

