### Control: tNFET Protocol

The control group will consist of patients, matched to the inclusion and exclusion criteria, who would have undergone tNFET at the RWH RSU. Patients undertake an ultrasound on days 10-12 of their cycle for those with a 28-day cycle. Upon detection of a dominant follicle of 18 mm or more and an endometrial thickness of 7 mm or more, serum LH and P4 are taken. An LH surge is defined as >25 IU/L in the context of P4 <5 nmol/L. Ovulation is defined as a P4 >5 nmol/L. LPS, in the form of a vaginal ORIPRO 200 mg pessary (Orion Laboratories Pty Ltd T/A Perrigo, Australia), is commenced on day 1 post ovulation, and embryo transfer is carried out 6 days post LH surge.

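### Removing enrolled women with progesterone above 5 nmol/L takes a feasibility failure out of a feasibility study, and the two groups are entered by unmatched rules

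*Protocol article*

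**What the plan says.** The aim in the Abstract (Objective) is feasibility: "This study aims to assess the feasibility of a progesterone-modified natural cycle protocol for FET". The primary outcome exists only for women who reach transfer: "The primary outcome will be the presence of a corpus luteum on ultrasound scans on the day of embryo transfer". Under Participants, "The study population will consist of 20 women undertaking FET cycles".

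Under Intervention: P4mNFET Protocol, blood is taken on the day the scan shows adequate endometrium and a 14.0 mm follicle. Then "should levels of P4 be under 5 nmol/L, exogenous P4 supplementation via vaginal pessary will then commence on the same day". Otherwise, "In the instances where P4 levels are greater than 5 nmol/L, the patient will be removed from the study".

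In the control pathway (Control: tNFET Protocol) the same threshold has another role: "Ovulation is defined as a P4 >5 nmol/L". Controls are identified in retrospect: "These controls would have undergone tNFET at the service provider within the preceding 12 months of the study start date". Study Type says that the secondary outcomes, namely clinic visits, biochemical pregnancy and clinical pregnancy, are compared with these controls. Implications ties the decision to run the randomised trial to the corpus luteum finding and sets no criterion on removals.

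**The concern.** Whether a woman can start is part of what a feasibility study measures. The method depends on reaching her after the follicle and endometrium qualify but before her own P4 rises. If that window is missed, the protocol has not worked for her, whatever happens to her clinically. The stated rule takes her out of the study after she has consented and been monitored, and nothing else in the article counts her.

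Two things are at stake. First, the planned noninferiority trial needs the share of monitored women who can use the protocol, for its eligibility and attrition assumptions, and this rule discards that figure. Because the decision to proceed looks only at the corpus luteum in women who reached transfer, a protocol that many women could not start might still pass. Second, the comparison of visits and pregnancy with controls sets side by side two groups that were entered by different rules.

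**Working it through.** **Inputs from the article.** 20 women in the intervention group (Participants); removal when P4 is above 5 nmol/L (Intervention); primary outcome assessed on transfer day only (Objective, Outcome Measures). The article states no power, precision target or dropout allowance behind the 20, so there is no figure of its own to reproduce.

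**Assumptions.** The share of women above 5 nmol/L, *q*, is not given; 5% to 30% is used for illustration. There are no other losses between starting P4 and transfer, and every transferred woman has a corpus luteum.

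**Step 1: is removal likely to occur at all?** P(at least one of 20) = 1 − (1 − *q*)^20. This gives 64% at *q* = 5%, 88% at 10%, 99% at 20% and over 99% at 30%.

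**Step 2: what does removal do to the figures?** With *r* removed and *x* women transferred with a corpus luteum, the rate among transfers is *x*/(20 − *r*) and the completion share among enrolled women is *x*/20. Intervals are exact (Clopper-Pearson) 95%.

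| *r* | Among transfers | Among all enrolled |
|---|---|---|
| 1 | 19/19 = 100% (82.4-100) | 19/20 = 95% (75.1-99.9) |
| 2 | 18/18 = 100% (81.5-100) | 18/20 = 90% (68.3-98.8) |
| 4 | 16/16 = 100% (79.4-100) | 16/20 = 80% (56.3-94.3) |
| 6 | 14/14 = 100% (76.8-100) | 14/20 = 70% (45.7-88.1) |

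Each removal costs 1/20 = 5 percentage points of completion, while the rate among transfers need not move.

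**Step 3: if removed women are replaced.** The article does not say whether they are. To reach 20 transfers at *q* = 20%, about 20/0.8 = 25 women must be enrolled. Completion is 20/25 = 80%, while the report would read 20/20.

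**Step 4: the entry rules side by side.**

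| | Intervention | Control |
|---|---|---|
| Identified | Prospectively, before monitoring results are known | Retrospectively, as having had tNFET |
| Blood taken at follicle of | 14.0 mm | 18 mm or more |
| P4 above 5 nmol/L | Ends participation | Defines ovulation |
| Transfer timed from | Start of study P4 | LH surge, which requires P4 below 5 nmol/L |
| Cycles stopped before transfer | Removed if stopped for P4 | Probably not selected |

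The two denominators are therefore conditioned by different rules. The table does not show which group this favours.

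**The case against.** The strongest reply is that the rule is a gate before treatment. It acts before any study P4 is given, the primary outcome is undefined without a transfer, and visits are defined as "the number of clinic visits required per patient undergoing this protocol". For the question of what happens once a woman starts, restricting the analysis to women who start is coherent. That stands, and it is why the figure among transfers should be kept. It does not answer the feasibility question, which includes whether she can start.

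A second reply is that being taken out of the study need not mean that her data are discarded, and that analysis sets are often left to a fuller document. This stands in part: the overstatement is certain only if these women leave the denominators. That is, however, the plain reading of the sentence, and the article contains nothing that offsets it.

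Three stronger readings are tempting and are not supported:

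- A reader might infer that controls at the same point go on to transfer. Blood is taken at different follicle sizes, and the article gives no transfer day for a control already above 5 nmol/L with no surge captured.
- A reader might infer that the corpus luteum rate is inflated. By the article's own control-group definition, women above 5 nmol/L have ovulated, so they are not evidence that the protocol prevents a corpus luteum. The two columns in Step 2 are different quantities.
- A reader might infer that the comparisons of visits and pregnancy are biased in favour of the new protocol. If controls also all reached transfer, pregnancy rates may rest on similar bases. A woman stopped at her first scan has few visits, so including her could lower the mean.

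**Conclusion.** The point holds in limited form. Removal after enrolment, on the plain reading, overstates the share of women in whom the protocol can be carried out, by 5 percentage points per removal out of 20. The true size is unknown because the article gives no frequency of P4 above 5 nmol/L; the range used is an assumption, and the intervals only illustrate how far the two figures could diverge. The comparison of secondary outcomes rests on unmatched entry rules, with the direction of bias not established. This should be fixed, since it bears on the study's declared aim and on the decision to proceed. It does not invalidate the primary outcome as defined.

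**What to change.** Leave the clinical handling of these women as it is and change what happens to their data.

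1. Replace the removal sentence with wording that these women do not start study P4 but stay in the study for data collection and analysis.
2. Add a feasibility outcome: among all women who start monitoring, the proportion who start P4 and reach transfer with a corpus luteum, with an exact 95% CI. Report the number stopped for P4 above 5 nmol/L.
3. Keep the corpus luteum proportion among transferred women as a separate figure, and consider both in the decision to proceed to the randomised trial.
4. Report visits and pregnancy per started monitoring cycle and per transfer. For the per-started-cycle comparison, select controls by started tNFET cycle, including cancelled ones.

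While editing, reconcile the two threshold sentences: a value of exactly 5 nmol/L falls under neither.

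The cost is a change of wording, retention of data already collected at the scan and blood visit, and slightly more record extraction for controls. The headline figure may look less favourable.

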**Figure 1 figure1:**
[figure not shown]
Visual representation of the patient journey with P4mNFET protocol. FET: frozen embryo transfer; hCG: human chorionic gonadotropin; P4: progesterone; P4mNFET: progesterone-modified natural cycle protocol for frozen embryo transfer; TVUS: transvaginal ultrasound.

### Control: tNFET Protocol

The control group will consist of patients, matched to the inclusion and exclusion criteria, who would have undergone tNFET at the RWH RSU. Patients undertake an ultrasound on days 10-12 of their cycle for those with a 28-day cycle. Upon detection of a dominant follicle of 18 mm or more and an endometrial thickness of 7 mm or more, serum LH and P4 are taken. An LH surge is defined as >25 IU/L in the context of P4 <5 nmol/L. Ovulation is defined as a P4 >5 nmol/L. LPS, in the form of a vaginal ORIPRO 200 mg pessary (Orion Laboratories Pty Ltd T/A Perrigo, Australia), is commenced on day 1 post ovulation, and embryo transfer is carried out 6 days post LH surge.

### Statistical Analysis and Sample Size

Given the qualitative and binary nature of the primary outcome, no statistical testing is proposed for this. Secondary outcomes will undergo *t* tests and Mann-Whitney *U* tests for data that are normally and not normally distributed, respectively. Should there be significant variation in the key baseline variables between the study and the control group, a multivariate analysis will be performed.

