## Methods

### Study Type

The proposed study will adopt a pilot cohort methodology consisting of 12 weeks of intervention and follow-up monitoring of participants for primary and secondary outcomes. Secondary outcomes will be compared with retrospective data from the tNFET control group.

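### Adjusting only when baseline differences are significant would often leave small-to-moderate confounding in the crude secondary comparisons of this nonrandomised 20 v 20 study

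*Protocol article*

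**What the plan says.** The design is stated plainly in Randomization: "This is a pilot prospective cohort study without randomization". Under Participants, "The study population will consist of 20 women undertaking FET cycles", and "The control group will consist of retrospective data from 20 women, matched against inclusion and exclusion criteria". Control: tNFET Protocol describes the controls in the same way, as "patients, matched to the inclusion and exclusion criteria, who would have undergone tNFET at the RWH RSU". Matching here therefore means meeting the same eligibility criteria. No pairing on age or any other named prognostic variable is described.

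Study Type confines the between-group comparison to the secondary outcomes: "Secondary outcomes will be compared with retrospective data from the tNFET control group". Statistical Analysis and Sample Size makes the default analysis unadjusted: "Secondary outcomes will undergo *t* tests and Mann-Whitney *U* tests for data that are normally and not normally distributed, respectively". It then sets the condition for anything further: "Should there be significant variation in the key baseline variables between the study and the control group, a multivariate analysis will be performed". It gives no level, test or size of difference that would count, and it does not list the variables. Limitations mentions the lower rigour of cohort studies and data-entry problems in the controls, but not confounding by baseline differences.

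**The concern.** Without randomisation, some difference in prognosis between the groups is to be expected. Whether a baseline difference is statistically significant depends heavily on the number of women. How far it biases the comparison depends on its size and on how strongly the variable predicts the outcome. With 20 per group the two can part company: a difference large enough to shift the estimate may be too small to be flagged, and the crude result then stands.

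The rule also lets the data choose the model. A reader cannot know beforehand whether the visit and pregnancy comparisons will be crude or adjusted, or for what.

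At stake is how far the secondary comparisons of visits and pregnancy can be trusted as background for the planned noninferiority trial.

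**Working it through.** The document gives no power, level or effect size, so there is no stated figure to reproduce. The check asks how often the trigger would fire.

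**Inputs.** From the document: n = 20 per group, not randomised, retrospective controls. Assumed: two-sided 5% level, two-sample t test on one continuous baseline variable, and a range of true standardised mean differences (SMD). The full 20 v 20 is kept as a best case, because the article also says "In the instances where P4 levels are greater than 5 nmol/L, the patient will be removed from the study", without stating replacement.

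**Smallest observed difference that triggers adjustment.** The standard error of a standardised difference is √(2/n) = √(2/20) = 0.316. The critical t on 38 degrees of freedom is 2.024. Threshold: 2.024 × 0.316 = 0.64 SD.

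**Chance of triggering on one variable.** Power is P(|T| > 2.024), where T is noncentral t with 38 df and noncentrality SMD × √(20/2) = 3.162 × SMD.

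| True SMD | Noncentrality | Flagged (5%) | Flagged (10%) | Flagged (20%) |
|---|---|---|---|---|
| 0.3 | 0.95 | 15% | 24% | 38% |
| 0.5 | 1.58 | 34% | 46% | 61% |
| 0.8 | 2.53 | 69% | 80% | 89% |

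At the 5% level, power reaches 50% at a true SMD of 0.64 and 80% at 0.91. For a binary variable at 50% v 30%, Fisher's exact test flags 16%; at 70% v 40% it flags 35%.

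**Sample size the screen would need for 80% power.** Normal approximation, n = 2(1.96 + 0.84)²/SMD², or about 15.7/SMD²: 15.7/0.09 gives 175 per group at 0.3 SD, and 15.7/0.25 gives 63 per group at 0.5 SD.

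**Several variables.** If k independent variables all carry the same imbalance, at least one is flagged with probability 1 − (1 − power)^k.
- SMD 0.5: 1 − 0.662³ = 71% for three variables, 1 − 0.662⁵ = 87% for five.
- SMD 0.3: 39% for three, 56% for five.
- No true imbalance: 1 − 0.95³ = 14% for three, 1 − 0.95⁵ = 23% for five.

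**Bias left in.** Simulation with 20,000 runs per scenario, one confounder, true group effect zero, and an assumed confounder–outcome correlation r of 0.3 or 0.5. Never adjusting gives a bias of r × SMD.

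| True SMD | Never adjust (r × SMD) | Adjust only if p < 0.05 | Always adjust |
|---|---|---|---|
| 0.3 | 0.09 to 0.15 | 0.05 to 0.09 | about 0 |
| 0.5 | 0.15 to 0.25 | 0.07 to 0.11 | about 0 |
| 0.8 | 0.24 to 0.40 | 0.04 to 0.07 | about 0 |

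All entries are in SD units; the always-adjust bias never exceeded 0.003. Type I error under the triggered rule was 5% to 6%.

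**Events available for a pregnancy model.** At an assumed 35% pregnancy rate, 40 × 0.35 = 14 events. Group plus age gives 14/2 = 7 events per coefficient; group plus two covariates gives 14/3 = 4.7.

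**The case against.** The strongest objection is that the article never says what significant means. Beside the tests named in the same section, statistical significance is the natural reading, but it is an inference. If the word means material, the power figures do not apply. That reading leaves the rule with no stated threshold, and naming a covariate in advance cures that too. The exact covariate list might reasonably sit in a fuller document, so its absence is not the point here. The conditional rule is what the article itself states.

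A reader might infer that real imbalance will usually go unadjusted, or that the worst-confounded comparisons are the ones left crude. The documents do not support either. Any observed difference of 0.64 SD or more triggers adjustment, so the largest realised imbalances are the ones dealt with, and the simulated bias is lower at 0.8 SD than at 0.5 SD. A failure rate above one half applies to a single variable with a true imbalance below about 0.64 SD. The article speaks of variables in the plural, and several moderate imbalances together would usually trip the rule.

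Restriction also helps. Both groups must be under 40, have a BMI of 18 to 35 and have regular cycles of 21 to 35 days. This narrows the possible imbalance, but still leaves room for groups that differ in age.

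Finally, the consequences are limited. The primary outcome has no between-group test, and Implications ties progression to the corpus luteum finding. The largest simulated bias is about a third of a standard error (0.11/0.32 = 0.34), and at an assumed 35% pregnancy rate the 95% half-width of a risk difference is 1.96 × √(2 × 0.35 × 0.65/20), about 30 percentage points. All of this stands. It lowers the weight of the point but does not make the trigger a sound rule.

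**Conclusion.** The point holds in a limited form. The stated rule makes adjustment depend on a screen that, at 20 v 20 and an assumed 5% level, misses a single 0.3 SD imbalance about 85% of the time and a 0.5 SD imbalance about 66%. Small-to-moderate confounding would often remain in the crude secondary estimates. Large imbalances, or several moderate ones, would more often be caught.

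The harm is residual bias of roughly 0.04 to 0.11 SD in the scenarios simulated, with little inflation of type I error. It is confined to visits and the two pregnancy rates. The level, the SMDs, the correlations and the 35% pregnancy rate are assumptions, since the document gives none of them. The change is worth making because it is nearly free, not because the study's main conclusion is at risk.

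**What to change.** - Delete the significance condition from Statistical Analysis and Sample Size.
- Prespecify age, as a continuous variable, as the adjustment covariate. It should be available in both groups, because it is an eligibility item and women whose inclusion information is missing are left out of the retrospective group. One covariate is as much as the expected number of events comfortably supports. Embryo stage is not shown to be held for the controls, so it should not be relied on.
- Report crude and age-adjusted estimates with 95% confidence intervals for every secondary outcome, whatever the baseline p-values. Linear regression would serve for visits, and Firth-penalised logistic regression for biochemical and clinical pregnancy because events are few.
- Describe baseline balance by standardised differences, without significance tests.
- Label the comparisons with the retrospective controls as exploratory.

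The cost is a change of wording and one extra model per outcome, with no new data. Intervals will be slightly wider. Penalisation reduces small-sample bias but adds no information, so the pregnancy estimates will stay imprecise.
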